#### Stroke impact scale (SIS)

The Stroke Impact Scale (SIS) 3.0 is a well-established 59-item interviewer-administered assessment of health-related quality of life for individuals after stroke [66,67]. The SIS captures 8 domains of function organized into subscales as well as an overall measure of perceived recovery from stroke. Both the full SIS 3.0 (ICF Participation level) and the hand function subscale (ICF Activity level) are used in ICARE as secondary outcome measures. The hand function subscale requires participants to indicate the difficulty experienced over the past 2 weeks with 5 activities involving the paretic hand, including: carrying heavy objects, turning a doorknob, opening a can or jar, tying a shoelace, and picking up a small coin.

### Other assessments

#### Monthly follow-up interviews

Within 30 days of randomization, the recruiting site team initiates monthly telephone interviews with each participant to ascertain information about health status, healthcare utilization, medications, other therapies, and adverse events.

#### Post-intervention interview

A multiple question survey interview is administered by a non-treating, unblinded member of the recruiting team upon completion of the intervention phase. At the post-intervention evaluation, each participant is asked a set of questions to assess the extent to which critical components of the investigational intervention (e.g. impairment mitigation, session intensity, participant chosen tasks, therapist-participant collaboration) were incorporated into each assigned therapy group [68].

#### Exit interview

At the final 1 year evaluation, participants complete another set of questions regarding activity since the end of the intervention phase. Participants are also asked to report the perceived value of the intervention and study participation.

### Usual care evaluation and treatment records

Receipt of usual and customary care, defined as outpatient occupational therapy (OT), is monitored and recorded from stroke onset to study endpoint. No more than six hours of outpatient occupational therapy treatment, excluding an OT initial evaluation, is permitted prior to randomization. Usual care in treatment hours is recorded at the time of randomization. Once randomized and through the end of the intervention observation window (16 weeks post-randomization), usual care is recorded at an individual session level for all treatment groups. Data include: 1) Date, 2) Length of treatment session in minutes, 3) Content, using CPT® codes, 4) Payer, 5) Location (at an ICARE site (on-site) or other therapy locations (off-site)), and 6) Change in (OT) prescriptions. Additional data collected include: initial prescription, all missed appointments and reason for absence, discharge and discharge reason. From these data, usual care dose, therapy content, attendance behaviors and reimbursement mechanisms can be used for secondary analyses. For therapy occurring off-site, all post-stroke outpatient OT records are procured with a signed HIPAA authorization. For therapy on-site, the Study Informed Consent and HIPAA authorization signed at screening permit internal access to these records. From the outpatient therapy records, the usual care data are gleaned during the intervention observation window. When a participant is randomized, he or she is provided with a monthly calendar up to the study endpoint and instructions to record all therapies attended, noting the date, time spent in therapy and type of therapy. These calendars are reviewed monthly during the telephone interview with the participant and provide the data collected regarding ancillary therapy utilization as well as outpatient OT received outside of the intervention observation window.

### Medication information

Data about medication prescription and usage are collected during pre-screening, screening, prior to baseline and at monthly intervals post-randomization. Prior to baseline, receipt of tPA (if known) is recorded and all prescribed medications are recorded by name. A participant-specific medication list is developed at the time of the Baseline assessment. Monthly, this list is revisited with the participant and updated accordingly. New medications are added at this time and data regarding discontinued medications are recorded. These data are intended to provide supplemental information about the medical and pharmacologic management of the ICARE sample.

### Standardization of assessments

All clinical research blinded evaluators (BE’s) must complete an initial certification (standardization) process for the WMFT and SIS, and maintain re-certification at least every 6 months, thereafter. A 3-day training workshop was conducted during the start-up phase, serving to introduce the BE’s to the standardized test protocols. Updated training materials include: printed manuals of test administration and scoring instructions; online video demonstration; peer review; practice with volunteers who have had a stroke; monthly training meetings; and an online discussion board. Certification is granted for performance of at least 90% mastery. The certifying therapist views a digital recording of test administration and scoring by the therapist seeking certification along with all assessment-specific study documentation; detailed verbal and written feedback are provided. All study personnel administering the National Institutes of Health Stroke Scale (NIHSS) [32,39,40] must obtain certification of standardized competency.

#### WMFT FAS rater panel

A panel of 3 experienced therapists provide FAS ratings for the WMFT. Inter-rater reliability is refined via teleconferences. The Data Management and Analysis Center (DMAC) convert and compress the site submitted edited digital WMFT test administration. Media stream access is provided to the members of the rater panel through the secure ICARE database website, thereby enabling remote viewing and scoring capability. Intra-rater reliability and inter-rater reliability were initially assessed using a sample of 8 videotaped WMFT test administrations procured from a database of previous studies. Raters rated each video at that time and after 1 month. A web/teleconference followed to review and discuss discrepant individual item ratings. This resulted in further refinement of the scoring guidelines. Two additional test-retest iterations were completed, each time with a set of 21 filmed ICARE WMFT test administrations. These were analyzed using weighted Kappa statistics, Spearman correlation coefficients and Bland-Altman plotting to determine points of disagreement. Currently, each of the 3 panel members rate each video independently, to yield 3 independent ratings per video. Specific instances of item score disagreement are identified by the DMAC for review and discussion by the panel before adjudication by majority vote. The WMFT FAS Panel meets via tele-conference monthly to view and rate a new video as a group.

### Randomization method

A stratified block randomization schema is used for each site to balance randomization assignment by motor severity and time from stroke onset. Participants are stratified using an ordered set of variables defined by: 1) baseline motor impairment using the Fugl-Meyer Upper Extremity motor score [49,69,70] (more impaired ≤ 35, less impaired ≥ 36, eligible range 19–58); and 2) days from stroke onset (early ≤ 59 days and late 60+ days, eligible range 14–106). No *a priori* assumptions are made about there being balance across stratification factors. Randomization assignment is obtained through the secure web-based data entry system, which confirms that all prerequisites have been completed before informing the CSC of the assignment. Each CSC maintains a randomization log at the site, and the DMAC maintains the master list for the trial. The balance of the group assignment is monitored weekly by the DMAC, and reported to the DSMB quarterly, with treatment group coded to maintain blinding.

### Interventions

#### Accelerated skill acquisition program

The Accelerated Skill Acquisition Program (ASAP) is a fully defined, principle-based protocol that integrates three fundamental elements including: **skill** acquisition through task-specific practice, impairment mitigation to increase **capacity**, and **motivational** enhancements to build self-confidence (Figure 2). ASAP is grounded in the evidence-based expectation that effective rehabilitation of the paretic upper extremity is achievable and based upon the provision of challenging, intensive, and meaningful task practice for motor skill acquisition, mitigation of associated linchpin impairments and dysfunctions of movement, and the confidence to integrate use of emerging skills into daily life activities [2,19,20,71,72].

**Figure 2 F2:**
[figure not shown]
**Conceptual model of the Accelerated Skill Acquisition Program (ASAP).** The conceptual model reflects ASAP’s intersecting emphases on skill acquisition, capacity building (impairment mitigation), and motivational enhancement. Challenging movement tasks are used as vehicles to address neurorehabilitation and recovery.

The ASAP structured protocol includes an initial evaluation and orientation session (Session A) and 30 1-hour visits of an individualized practice program focused on function of the arm and hand most affected by the stroke. This integrated and evidence-based intervention for upper extremity recovery arose from diverse but converging, complementary, and interdisciplinary literatures of basic and applied science as well as recent translational and stroke clinical trial research of upper extremity recovery. Unique aspects include the structured framework by which intensity and progression of practice is managed and which fosters participant skills and confidence through therapist-patient collaboration. Participants randomized to ASAP are given a customized package of therapy that includes challenging, intensive, and meaningful practice of activities related to participant chosen real-world tasks (e.g., carrying groceries, handwriting) that engage the arm most affected by the stroke. Participants are offered a mitt to wear on the less affected hand during the time outside of therapy to promote use of the weaker arm and hand; however, the participant is not required to use the mitt if so chosen. Outside of therapy specific assignments (i.e., Action Plans) are given to encourage self-managed, confident, safe, and effective arm use at home and in the community.

Table 4 summarizes the eight evidence-based, non-exclusive (over-lapping) operating principles that are currently used to guide ASAP intervention sessions: 1) ensure challenging and meaningful practice [20,73-76], 2) address important mutable impairments through task-breakdown [77-80], 3) enhance motor capacity through overload and specificity [81,82], 4) preserve natural goal-directedness in movement organization [83,84], 5) try to avoid artificial task breakdown when engaging in task-specific practice [85], 6) assure active patient involvement and opportunities for self-direction [86,87], 7) balance immediate and future needs for efficient motor skill and capacity enhancement with the development of confidence and self-management skills [88,89] and 8) drive task-specific self-confidence (self-efficacy) high through performance accomplishments [90,91]. Together, these principles are designed to emphasize and drive the development of skilled movement performance.

**Table 4 T4:** ASAP’s eight overlapping operating principles

	**Principle**
1	Ensure challenging and meaningful practice
2	Address important (interfering) changeable impairments
3	Enhance motor capacity through overload and specificity
4	Preserve natural goal-directedness in movement organization
5	Avoid artificial task breakdowns when possible
6	Assure active patient involvement and opportunities for self-direction
7	Balance immediate and future needs
8	Drive task-specific self-confidence high through performance accomplishments

#### ASAP protocol parameters

The program begins with an orientation and evaluation session to accomplish the following 10 goals: 1) prepare the collaborative ‘real-world’ task list to be used during training; it includes 6 tasks the patient most wants to perform with at least two bimanual activities, two strength-dependent activities including the most affected arm, and two activities requiring dexterity of the most affected hand, 2) designate a priority or benchmark task from the collaborative task list, 3) determine fundamental impairments and the priority-task challenge threshold or movement breakdown point(s), 4) prepare a collaborative schedule for the first day of training, 5) orient the participant to the mitt and its function including safety precautions, 6) identify appropriate conditions for mitt wearing and not wearing, 7) orient the participant to a recurring brief self-efficacy question, 8) orient the participant to out-of-lab action plans, 9) orient the participant to their collaborative role with the trainer and 10) obtain the participant’s agreement to be a collaborative partner. The orientation and evaluation Session A may last up to two full hours.

Training sessions are to be 1 hour per day, 3 times per week for a total of 30 hours, with rest breaks allowed to maximize engaged time-on-task. Following a debriefing of the previously assigned Action Plan and the acquisition of several physiologic measures (i.e., BP, heart rate, pain, muscle soreness), each regular training session begins with a collaborative ordering of the real-world tasks identified during Session A (orientation and evaluation). The real-world tasks may change as interests and goals evolve over the 30 sessions, however the priority task may not change for benchmarking purposes. Task and movement analysis are done for each real-world task to determine the key movement dysfunctions or impairments. The goal of intervention training is to focus attention and effort directly on the problematic area (i.e. dysfunction, impairment) to facilitate skill acquisition without simply providing a compensatory strategy as an easy and quick fix to the problem. Classic exercise-overload principles (e.g. intensity, periodicity) are used to drive progression and build motor capacity (e.g., muscular strength and endurance, coordination). Practice activities within the three categories of real-world functional tasks (i.e., strength, dexterity, bimanual) are selected based on patient task preferences. Training is collaborative and interactive with the participant providing problem identification as feasible (e.g., “What is the limiting factor when you perform that task?”) and solutions through self-assessment and trainer feedback/suggestions. Confidence building and empowerment are embedded in the training and education during each session. Task-specific (i.e., priority task) self-efficacy assessment is performed 4 times throughout the 30 sessions using a Brief Self-Efficacy Rating Scale. The participant is asked to provide a number between 0 and 10 in response to the question: “How confident are you that you can (fill in specific priority task activity)?” The confidence rating is followed by a question asking, “What can we do this week to increase your capabilities and raise your confidence?” As the participant gains insight and develops self-assessment and management skills, the response to the follow-up question is expected to become more insightful and rich in self-knowledge and ways to drive challenge and improvement. One strategy for building capacity is to perform inter-session ‘Action Plans’ or out of clinic activities. All 30 sessions have associated Action Plans including some with handouts that provide background information related to ASAP principles and evidence. Table 5 lists the knowledge-based handouts provided to participants and the planned distribution order across the 30 sessions. Individual participant-specific Action Plans are also generated and used throughout the 30 sessions. These Action Plans encourage specific practice in the home or community settings. Examples include finding a challenging task involving food preparation or eating or reading an education handout about motor recovery. At the beginning of each session, participants are asked to report on the effectiveness of their Action Plan activities on the next day of training. The therapist also rates the participant’s engagement in the Action Plan on a scale from 1 = no effort/did not attempt, 2 = some effort, and 3 = great effort/engagement, apparently practiced diligently.

**Table 5 T5:** List of standard action plans with handouts

1.	Using the soft mitt on the better hand
2.	Preventing arm and hand injuries while training
3.	Family and friend support
4.	Helpful thoughts for performing challenging activities in public
5.	Getting the most learning for your efforts (Motor learning Part I)
6.	Turning science into skill (Motor learning Part II)

Figure 3 illustrates the clinic environment and two examples of tasks selected by participants to practice during ASAP sessions. To prevent cross-contamination between study groups, further details of the investigational intervention as outlined in the ASAP MOP have been embargoed until study completion.

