### Type of design

ICARE is a parallel group, three arm, single blind, phase III, superiority, randomized, controlled trial of a principle-based upper extremity training program provided in the outpatient setting after the acute hospitalization phase. Once discharged from an inpatient or acute setting and following baseline assessment, participants are randomized, no earlier than 14 days and no later than 106 days after stroke onset, to one of three intervention groups: ASAP, DEUCC or UCC. The primary outcome, collected at 1 year post-randomization, is the log WMFT time score. The secondary outcomes are the SIS hand domain subscale and the full SIS scores. To prevent unintended crossover, details of the ASAP protocol are currently embargoed; therapists who provide ASAP sign a confidentiality and nondisclosure agreement and do not provide UCC or DEUCC treatments. Outcome assessors are blinded to treatment group. The study flow is illustrated in Figure 1.

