#### Usual and customary care (UCC)

The UCC group receives Outpatient Occupational Therapy for the upper extremity as determined by each participant’s individual occupational therapist, based upon usual and customary practice standards. In accordance with those practices, the participant attends a standard Occupational Therapy evaluation session prior to initiating intervention sessions (treatment). The number of visits and frequency (dose) for the intervention is determined per the therapy prescription generated at the evaluation, site-specific usual and customary practices, and payer guidelines (e.g. private insurance, HMO, Medicare). The evaluation may have occurred prior to randomization. The dose may be modified per usual and customary practices as the intervention ensues. The treating therapist(s) documents each session per the treating facility’s protocol and documentation methods. The CSC of the clinic that randomized the participant is responsible for procuring the evaluation and treatment records and gleaning the necessary information for ICARE using standardized forms. Vital signs, as well as any symptoms of fatigue or stress are monitored during each session in accordance with usual and customary standard practice.

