The Data Safety and Monitoring Board (DSMB) is appointed by the NINDS to ensure highest quality and ethical study execution and consists of a stroke neurologist, a physical therapist, a rehabilitation neurologist, a biostatistician, and an NINDS DSMB liaison. The DSMB evaluates a full study report, prepared by the DMAC Director and Project Manager, biannually. This report provides a summary of study activities, issues and progress since the last report in narrative form followed by data tables and figures, which include grouped data sets, blinded for treatment allocation. As an appendix to the report, each site prepares a site-specific narrative including proactive strategies for any areas of concern. Both the main report and the site-specific reports address the primary issues of: participant accrual, execution of intervention adherence (ASAP & DEUCC only), retention, safety and data quality, including missing data, protocol adherence, and safety. An abbreviated report is evaluated by the DSMB during the interceding quarters. The DSMB monitors serious adverse events and reviews cumulative adverse event data quarterly to ensure study safety. These data are also grouped, but blinded for treatment allocation. The DMAC Director prepares unblinded reports and analyses if requested by the DSMB. The DSMB meets biannually with the Executive Committee, DMAC Director, and MSM, alternating between tele-conference and in person meetings per annum. Additional meetings may be scheduled at the discretion of the DSMB or NINDS.

An independent Medical Safety Monitor (MSM) is chosen by the NINDS staff and the Executive Committee. This rehabilitation physician is responsible for timely review and adjudication of all serious adverse events and for reviewing summary reports of all adverse events on a regular basis. The MSM attends the annual DSMB meetings as well as the quarterly phone meetings.

The Clinical Site Coordinator (CSC) Committee consists of the Project Manager, and seven Clinical Site Coordinators; a DMAC member, PI#1 and other study personnel join as needed. This committee is responsible for collaborative training and problem-solving; recruitment, protocol implementation; data entry; resolution of site differences and assurance of trial consistency. This committee meets twice monthly.

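### Between-arm comparison of non-serious adverse events is at risk of detection bias, probably against ASAP, because symptoms are trial-recorded at each session only in that arm

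*Protocol article*

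**What the plan says.** All references are to the protocol article.

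- **ASAP sessions.** The section on ASAP protocol parameters describes what precedes training on each day: "the acquisition of several physiologic measures (i.e., BP, heart rate, pain, muscle soreness), each regular training session begins". There are 30 such sessions. The therapists are certified by the trial and work in this arm only: "therapists who provide ASAP sign a confidentiality and nondisclosure agreement and do not provide UCC or DEUCC treatments" (Type of design).
- **UCC sessions.** Monitoring is described as follows: "Vital signs, as well as any symptoms of fatigue or stress are monitored during each session in accordance with usual and customary standard practice". On the record itself: "The treating therapist(s) documents each session per the treating facility’s protocol and documentation methods". The clinical site coordinator is then "responsible for procuring the evaluation and treatment records and gleaning the necessary information for ICARE using standardized forms".
- **DEUCC sessions.** The DEUCC section sets the same 30 hours as ASAP and states that documentation and data collection are identical to UCC.
- **What is extracted from therapy records.** The section on usual care evaluation and treatment records begins its list: "Data include: 1) Date, 2) Length of treatment session in minutes, 3) Content, using CPT® codes, 4) Payer". It goes on to location (on-site or off-site) and prescription changes, with missed appointments, discharge and the reasons for each. No symptom or adverse event item is listed.
- **Inquiry common to all arms.** Under Monthly follow-up interviews: "the recruiting site team initiates monthly telephone interviews with each participant to ascertain information about health status, healthcare utilization, medications, other therapies, and adverse events".
- **Reporting and review.** A site team member files a report within 24 hours of learning of an event, and the medical safety monitor adjudicates serious events. On the cumulative data that the DSMB reviews each quarter: "These data are also grouped, but blinded for treatment allocation".

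**The concern.** Non-serious events are counted when someone connected with the trial learns of them. In ASAP, a trial therapist asks about pain and soreness and measures blood pressure at every visit. In the other two arms, an event noticed in therapy is written in a facility record, if at all, and the one explicit adverse event inquiry is a monthly call. Several of the expected non-serious events listed under Adverse event monitoring and reporting are ones that the ASAP checks can bring to light: soreness or pain lasting beyond 48 hours, shoulder pain and excessive blood pressure responses.

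If detection differs, ASAP could show an excess of minor events when the true rates are equal, or a true excess in DEUCC could be masked. At stake are the DSMB's reading of coded groups and the tolerability statement in the final report. The efficacy analysis is not affected.

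**Working it through.** The article gives no adverse event rate, no planned test of adverse events and no power for harms, so there is no stated figure to reproduce. The check compares the routes by arm and then gives a scale on assumed values.

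**Step 1: routes by which a non-serious event can reach the database**

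| Route | ASAP | DEUCC | UCC |
|---|---|---|---|
| Monthly interview asking about adverse events | yes | yes | yes |
| Therapy sessions in the window | 30 | 30 hours, 30 sessions scheduled | not fixed |
| Pain and soreness named for each session | yes | no | no |
| Vital signs at sessions | yes, blood pressure and heart rate | yes, to usual practice | yes, to usual practice |
| Fatigue or stress symptoms at sessions | not named | yes, to usual practice | yes, to usual practice |
| Who records | trial-certified therapist | treating therapist, facility methods | treating therapist, facility methods |
| Absence and discharge reasons | usual-care sessions only | yes | yes |

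The DEUCC monitoring entries assume that the UCC description carries over, since the DEUCC section makes content and documentation identical.

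Over the 16-week window, the monthly interview gives 16 × 7 / 30.4 = 3.7, or about 4 calls, in every arm. The contrast between ASAP and DEUCC is thus not one of session numbers. It lies in which symptoms are asked about, who records them and whether the record is a trial record. UCC may also differ in the number of sessions.

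**Step 2: direction**

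Reports start from a site team member's knowledge. An ASAP therapist is trained and certified by the trial. An off-site occupational therapist is not evidently part of the site team (an inference; the article does not say). Pain and soreness are therefore likelier to be reported from ASAP.

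**Step 3: scale, on assumed values only**

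Let the true risk p be equal in both arms, with 120 per arm and detection probabilities dA (ASAP) and dC (comparator).

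- Expected counts: 120 × p × dA and 120 × p × dC.
- Spurious risk ratio: dA / dC, whatever p is.
- Chance of a nominally significant excess in ASAP: Φ[(p1 − p2 − 1.96 × SE0) / SE1], with p1 = p·dA, p2 = p·dC, p̄ = (p1 + p2)/2, SE0 = √(2p̄(1 − p̄)/120) and SE1 = √([p1(1 − p1) + p2(1 − p2)]/120). With equal detection it is 2.5%.

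| dA, dC | Risk ratio | Expected events at p = 0.20 | Chance at p = 0.10 | p = 0.20 | p = 0.30 |
|---|---|---|---|---|---|
| 0.95, 0.90 | 1.06 | 22.8 v 21.6 | 3% | 4% | 4% |
| 0.90, 0.70 | 1.29 | 21.6 v 16.8 | 8% | 13% | 19% |
| 0.90, 0.50 | 1.80 | 21.6 v 12.0 | 23% | 43% | 63% |

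Worked line (p = 0.20; 0.90 v 0.50): p1 = 0.18, p2 = 0.10, SE0 = 0.0448, SE1 = 0.0445; (0.08 − 1.96 × 0.0448)/0.0445 = −0.18, so Φ is about 0.43.

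None of these values of p, dA or dC comes from the article.

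**The case against.** The other side has several sound points.

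- The ASAP text describes physiologic measures taken before training. It does not describe an adverse event inquiry. The explicit inquiry is the monthly call, which is the same in every arm, as are the reporting form and its time limit.
- Vital signs, fatigue and stress are monitored at each usual-care session, so a blood pressure response can be seen there too. The clearest gap is in pain and soreness.
- A reader might count about 35 trial contacts in ASAP (Session A, 30 sessions, about 4 calls) against about 4 elsewhere. That leaves out on-site DEUCC and UCC therapy and the evaluations common to all arms. The article does not give the off-site share.
- A reader might infer that events noted in usual-care sessions are never captured. The listed items come from a section on dose, content and payer. The extraction forms and the Manual of Procedures are not shown, and absence and discharge reasons could reveal an event.
- A reader might think that expected events worded around study participation or a treatment day cannot be recorded in UCC. Those items classify expectedness. The definition of an adverse event covers any new or worsened event, so rewording them would change little.
- No formal adverse event test by arm is planned.

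These points narrow the concern but do not remove it. Pain and soreness are named for session recording in ASAP alone, the recorder differs by arm, and equal hours in DEUCC do not make the recording equal. Coding the groups for the DSMB protects the blind but does not correct unequal detection.

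**Conclusion.** The by-arm view of non-serious adverse events is at risk of detection bias, and the likely direction is against ASAP. The text supports a risk; it does not show that bias has occurred. A reader might infer that the whole harms comparison is biased, but serious events such as death or hospitalization are unlikely to be missed by monthly calls, and an independent monitor adjudicates them.

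The size cannot be derived. Assumed detection from 0.95 v 0.90 to 0.90 v 0.50 gives spurious risk ratios of 1.06 to 1.80, that is, from negligible to misleading, and nothing in the article favours one end.

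The conclusion rests on two further assumptions: that the grouped DSMB data are shown by coded arm, which is likely because the Randomization method section describes coded groups in DSMB reports, and that no uniform session-level adverse event checklist exists in the unseen Manual of Procedures.

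**What to change.** 1. Record the source of each adverse event: monthly interview, therapy session or other. Allow more than one source, so that an event first seen at a session and also reported at interview counts under both.
2. For the DSMB and the final report, base the between-arm reading of non-serious events on those elicited at the monthly interview.
3. Compare serious events from all sources.
4. Still show all-source totals and session-found events by arm, labelled as not equally ascertained. Removing session-found events altogether could hide true treatment-related harm.

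The cost is one extra field, one extra table and fewer events in the common-source comparison. The article reports that enrolment was still open and the interim analysis done. A source field labels events without changing how they are sought, so it does not make ascertainment inconsistent over time. For events already reported, the source would have to be taken from the existing report or marked unknown. One limit remains: participants asked about pain at every session may be readier to mention it on the call, so the common-source comparison reduces the bias but may not remove it.
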